### Procedures

Families who are interested to participate in the TRACE study are informed via telephone and information letters (sent via e-mail). Families can choose whether they want to participate in the dietary treatment arms or the CAU arm. If they choose a dietary treatment, they will be randomly assigned to either the elimination diet or the healthy diet.

If the eligibility criteria are met, parents are invited for an intake with a researcher to explain further details of participation, plan appointments and to disclose which diet the child is randomized to via a sealed envelope. Both parents fill out a written informed consent for the TRACE study (Additional file 1). If children are 12 years old, they also need to sign the consent forms. In addition, teachers are informed about the study via e-mail and general practitioners via postal letters.

Assessments will take place at baseline (T0), after five weeks of treatment (T1), after four (T2), eight (T3) and 12 (T4) months after start of treatment (i.e. dietary treatment or CAU). T0 will be scheduled within two weeks prior to the start of the treatment. Medication treatment prior to the dietary treatment has to be discontinued no later than one week before start of the diet. T0, T1 and T4 assessments will take place at one of the two participating sites. For the T2 and T3 assessments, parents are asked to fill out questionnaires online. Teachers are asked to fill out online questionnaires at T0, T1 and T4. Figure 1 depicts a flowchart on recruitment and procedure of the study.

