## Methods

### Participants

Families are recruited at two clinical centers in the Netherlands: Karakter Child and Adolescent Psychiatry (Nijmegen) and Triversum - GGZ-NHN Child and Adolescent Psychiatry (Alkmaar). Researchers will screen files of patients (after consent of parents and/or psychiatrists) within these centers in order to check for eligibility or psychiatrists will refer the patients to the study. In addition, participants are recruited at the national level via advertisements, newspapers, the TRACE website, flyers and social media. Moreover, general practitioners, dieticians and other psychiatric institutions act as ambassadors and collaborate in the recruitment process by referring patients to the study. At the Nijmegen site, there is a team of certified clinicians who can diagnose (if necessary) participants recruited outside the participating centers.

For eligibility, participants must meet the following criteria: ADHD diagnosis according to the DSM-5 (any presentation) and 5–12 years old at the inclusion date. Comorbidities are allowed except for eating disorders (i.e. anorexia or bulimia nervosa) and diabetes mellitus. Exclusion criteria are insufficient mastery of Dutch language in parents or children; current treatment for ADHD that cannot be discontinued; significant parent-child relationship problems requiring family therapy; unwillingness to have meat or animal food products in the diet (without these products it is impossible to achieve nutritional adequacy of the overall diet for participants in the ED group). The CAU participants need to fulfill the same inclusion- and exclusion criteria.

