### Study design

#### Randomization

Originally, the TRACE study was a three arm randomized controlled trial: participants were randomized to an elimination diet, healthy diet or CAU. However, randomization across a dietary intervention versus CAU proved not feasible. Parents usually had a strong preference towards either a dietary intervention or CAU. This resulted in an extremely slow inclusion rate, a high number of drop-outs and thereby unrepresentative groups of CAU. Therefore, after inclusion of 17 participants, the design was changed into a two arm randomized controlled trial (elimination diet vs. healthy diet) with a non-randomized comparator arm (CAU). Participants interested in a dietary intervention are randomized (50:50) to either an ED or a healthy diet with randomization within each participating center. Randomization by means of minimization is performed, including sex and age as factors, resulting in four groups. Within each group, blocked randomization is used (block size eight). The non-randomized comparator arm includes children who are being treated with CAU. Researchers disclose the group allocation to parents via a sealed envelope. Participants, researchers and dieticians are aware of treatment allocation. Researchers who will code the behavior observation (see secondary outcomes) are blinded to group allocation and time of assignment.

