### Statistical analyses

All primary analyses will be Intention To Treat. The primary outcome will be measured as an ordinal variable with five categories. Therefore, the effect of the intervention will be measured in terms of odds ratio, comparing odds for reducing ADHD symptoms and emotion dysregulation symptoms in the elimination diet group with the corresponding odds in the healthy diet group. Multiple logistic regression analyses will performed to compute the odds ratio and 95% confidence intervals, using ordinal logistic regression analysis. The CAU group will be used as a reference group.

Differences in continuous outcome measures between the dietary trajectories will be determined with analyses of ANCOVA. The follow-up value (T1, after five weeks) will be added as the dependent variable and the baseline value will be added as covariate. The two dietary groups will be compared on all outcomes at T1, using T0 scores as covariates. Clinical significance will be estimated using the partial eta squared effect. The CAU group will be used as a reference group.

In addition, a repeated measures ANOVA will be performed. First, the whole sample will be used (Intention to Treat) to determine whether adding a dietary treatment has beneficial outcomes on costs and effects of the whole treatment trajectory after 12 months (regardless of continuing the dietary treatment after 5 weeks or not). Next, per-protocol and post-hoc analyses will be performed using repeated measures ANOVA where the main outcome measures will be compared across the three conditions (i.e. elimination diet; healthy diet; CAU). Also, we will determine how many children adhered to the diet after 12 months, whether the intervention effects maintained after 12 months, which products are eliminated from the diet after 12 months and the nutritional quality of the attained diet after 12 months.

Finally, two moderator analyses will be performed: one comparing dietary responders versus non-responders (predicting respondership) and another comparing children/families adhering to a dietary treatment versus children/families that are not able to do so (predicting adherence). Both moderator analyses will be performed to compare children/families after 5 weeks and after 1 year of treatment.

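### The article does not place written consent before allocation and its disclosure, and fixes a block size of eight among staff who know the allocations, which leaves room for entry to depend on the allocated diet

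*Protocol article*

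**What the plan says.** Protocol article, Procedures: "Families who are interested to participate in the TRACE study are informed via telephone and information letters (sent via e-mail"), and they choose between the dietary arms and care as usual (CAU). Those who meet the eligibility criteria and chose a diet come to an intake with a researcher. Its purposes are to explain further details, "plan appointments and to disclose which diet the child is randomized to via a sealed envelope". The next sentence reads "Both parents fill out a written informed consent for the TRACE study", without a time relative to randomisation or to opening the envelope.

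Participants: the only other consent mentioned concerns access to records: "Researchers will screen files of patients (after consent of parents and/or psychiatrists) within these centers". The same section has researchers confirm the ADHD diagnosis by a structured interview with the parents.

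Randomization: allocation is 50:50 within each centre, with sex and age forming four groups. "Within each group, blocked randomization is used (block size eight"). Disclosure by sealed envelope is repeated, and "Participants, researchers and dieticians are aware of treatment allocation".

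Statistical analyses: "All primary analyses will be Intention To Treat". The article does not say from which moment a child belongs to that set.

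**The concern.** An intention-to-treat comparison keeps the protection of randomisation only if every child who receives an allocation is counted. If a family can learn its diet before signing, and an unsigned family is not counted, entry may depend on the diet drawn. The two groups of 81 would then be selected after disclosure. The two diets are visibly different offers, so a preference between them is plausible.

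The second exposure acts before allocation. Staff who know past allocations in a stratum and the block size can sometimes foresee the next one. Some exclusion criteria need judgement, such as relationship problems that require family therapy, or ADHD treatment that cannot be discontinued. Foreknowledge could therefore influence who is judged eligible and when.

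**Working it through.** **Order of steps.** No arithmetic applies; the statements are set side by side.

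- Procedures speaks of the diet the child is already randomised to when the intake takes place, so the allocation appears to exist by then.
- Consent follows in a separate sentence without a time.
- The consent in Participants covers file screening, not the trial.
- Randomization and Statistical analyses add nothing on when consent is signed or on children whose family declines after disclosure.

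The text is compatible with consent before the envelope is opened and with consent after it. It secures neither.

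**Predictability of blocks.** Inputs: block of eight at 50:50, so m = 4 per diet; two centres; four sex/age groups; 162 children.

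- Certain allocations in a complete block: 2m/(m+1) = 8/5 = 1.6 of 8 = 20%.
- Expected correct guesses in a complete block, always guessing the diet with more places left: 4 + (256/70 − 1)/2 = 5.33 of 8, about 67%.
- Stratum size if strata fill equally (assumption): 162/(2 × 4) ≈ 20, which is two complete blocks and half of a third.
- Certain: 2 × 1.6 = 3.2 of 20 = 16%. The half block adds none, because at most four places of one diet are used up by its end.
- Correct guesses in the half block, place by place: 0.500 + 0.571 + 0.571 + 0.629 = 2.27. Total (2 × 5.33 + 2.27)/20 = 12.93/20 = 64.6%.

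So about 16–20% of allocations are certain and about 65–67% can be guessed, for a person who knows the block size and tracks the stratum.

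**What selective refusal could do.** The plan's own power was reproduced first, with 81 per arm, two-sided α = 0.05 and the five categories of Table 4. The methods were a simulated tie-corrected Wilcoxon test (20,000 runs) and the Whitehead proportional-odds formula.

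- Scenario 1: 0.991–0.996 (stated 0.99).
- Scenario 2: 0.651 and 0.656 from the counts, 0.616 and 0.624 from the rounded percentages (stated 0.64).

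The model therefore matches the plan. The documents give no refusal rate, so what follows is illustration. Assume no true difference: both arms have the Table 4 healthy-diet distribution (10, 30, 25, 20, 15%). A fraction d of elimination-diet (ED) families declines after disclosure and is not analysed, and all of them would have been non-responders or deteriorated. For d = 10% the two worst categories lose 0.10 in the ratio 20:15, leaving 0.143 and 0.107. Dividing all five by 0.90 gives an analysed ED distribution of 11.1, 33.3, 27.8, 15.9, 11.9%.

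| d | Odds ratio under no effect | Type I error |
|---|---|---|
| 5% | 1.12 | 0.06–0.07 |
| 10% | 1.26 | 0.12–0.13 |
| 15% | 1.45 | 0.24–0.27 |
| 20% | 1.70 | 0.42–0.46 |

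The ranges cover replacing decliners up to 81 or not replacing them (8,000 runs each). If refusal is unrelated to outcome, the type I error stays near 0.05. Unrelated loss of 5, 10 and 20% in both arms then costs only power: scenario 2, from the percentages, falls from about 0.62 to 0.60, 0.57 and 0.52.

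**The case against.** The strongest reply is that the article never says consent comes last. The sentence on parental consent is followed by ones on the signature of 12-year-olds and on informing teachers and general practitioners, which reads as a list of topics. An allocation kept in a sealed envelope until the form is signed does not allow refusal by diet. The flowchart (Fig. 1) and the consent material are not shown, and an article condenses its protocol. All of this stands, and so the point is about what the text secures, not about what was done.

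Several stronger readings are tempting and not supported:

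- A reader might infer that participation is first explained at the intake. Families were informed earlier by telephone and letter, and the intake adds details.
- A reader might infer that decliners leave the intention-to-treat set. The set is not defined; if consent precedes opening, later refusers are randomised participants and belong in it.
- A reader might take the strong preferences and drop-outs reported under Randomization as evidence of preference between the diets. They concerned a diet versus CAU, a contrast that is no longer randomised.
- A reader might conclude that later allocations in a block are known. Only about 16–20% are certain, and only to someone who tracks the stratum. No section says that screening staff do so. Eligibility also has fixed symptom thresholds with teacher input, which limits discretion.
- A reader might add that all primary-outcome ratings are unblinded. Teachers are not listed among those aware of allocation, and rater blinding does not bear on who enters.

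What the reply does not remove: the article chose to describe this sequence, and no statement in it puts consent before allocation or disclosure.

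**Conclusion.** The point holds as an exposure, not as a demonstrated bias. As described, the allocation exists by the intake, consent is not secured before it or before disclosure, and the analysis set is not tied to the moment of allocation. The fixed block of eight adds a modest predictability: about 16–20% certain and 65–67% guessable against 50%, assuming equally filled strata and a person who tracks them.

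No size of bias can be derived from the documents. The type I error ranges from about 0.05, if refusal is unrelated to outcome, to about 0.12–0.13 if 10% of ED families decline and every one would have had a poor outcome. The latter is a worst case, not an estimate. By symmetry, such refusal in the healthy-diet arm would act in the opposite direction. Because the remedy costs little and protects the randomised comparison, it is worth making.

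**What to change.** In Randomization and Procedures, set the order: eligibility recorded, written consent of both parents, allocation, disclosure. State that every child allocated from then on is counted in the intention-to-treat set, whatever the family decides after the envelope is opened.

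For the remaining recruitment, use varying block sizes that are not disclosed to recruiting researchers. Concealment matters as much as variation: in a complete block of known size the certain share is 1/(m+1), which is 1/5 for blocks of eight and 1/3 for blocks of four (m = 2).

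For families already recruited, report by diet how many declined after disclosure. If consent has always preceded the opening of the envelope, one sentence saying so, with these counts, settles the question of refusal.

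Cost: a new allocation list and a slightly longer intake. The article appeared in May 2020 and expects recruitment to end in December 2020, so the change can still reach the remaining families.

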#### Primary outcome

##### Respondership

Parents and teachers are invited to rate the child’s ADHD traits using the SWAN questionnaire. The SWAN consists of 18 DSM-IV-based items scored on a 7-point Likert scale ranging from 3 (*far below average*) to -3 (*far above average*) with higher scores reflecting more severe ADHD symptoms [21]. Items 1 to 9 assess symptoms of the ADHD inattentive type and items 10 to 18 assess symptoms of the ADHD hyperactive/impulsive type. The Dutch version of the SWAN questionnaire is a reliable instrument (Cronbach’s α = .87) [28, 29] and demonstrates adequate convergent and discriminant validity [28, 29]. Parents and teachers also are asked to fill out the Strengths and Difficulties Questionnaire (SDQ) to assess emotion dysregulation [30]. The SDQ Dysregulation Profile (SDQ-DP) includes fifteen items representing emotional symptoms, conduct problems and hyperactivity-inattention [31]. The items can be answered on a 3-point scale ranging from 0 (*not true*) to 2 (*definitely true*) with higher scores indicating more emotion dysregulation problems. The Dutch version of the SDQ-DP demonstrates adequate reliability (Cronbach’s α = .85) and construct and longitudinal validity [31].

To align with the evaluation of the diet after 5 weeks, response to treatment will be evaluated by assessing the change in ADHD and emotion dysregulation symptoms at T0 and T1 or T4 (i.e. SWAN inattentive scale, SWAN hyperactive/impulsive scale and SDQ dysregulation profile rated by both parent and teacher: together six scales) [32]. A 30% or more symptom decrease will be regarded as a significant response to treatment (i.e. positive value), and a 30% or more symptom increase is regarded as significant deterioration of symptoms (i.e. negative value) [9, 33]. The primary outcome variable ‘respondership’ is divided into five categories:
Full responder (significant response on both parent and teacher rated scales): all scales are ≥ − 20% AND at least one of three parent rated scales shows a ≥ 30% symptom reduction AND at least one of three teacher rated scales shows a ≥ 30% symptom reduction.Partial responder (significant response on parent or teacher rated scale):

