#### Descriptives

##### Prior beliefs

Parents prior beliefs about the short-term and long-term success and burden of dietary intervention and CAU are evaluated using a 5-item questionnaire in which parents rate their prior beliefs on a 5-point scale ranging from 0 (*completely disagree*) to 5 (*completely agree*). This measurement also will be used to examine successful randomization, by verifying whether the three groups differ in beliefs about the effectiveness of the intervention at baseline.

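### Parents probably rate T0 knowing the allocated diet, and T0 is not tied to the medication stop, so the baseline for percent change can be biased or not comparable with T1

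*Protocol article*

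**What the plan says.** All from the protocol article.

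- **Disclosure (Procedures).** Eligible families come to an intake, where the researcher is to "plan appointments and to disclose which diet the child is randomized to via a sealed envelope". Under Randomization: "Participants, researchers and dieticians are aware of treatment allocation".
- **T0 window (Procedures).** "T0 will be scheduled within two weeks prior to the start of the treatment".
- **Medication (Procedures).** "Medication treatment prior to the dietary treatment has to be discontinued no later than one week before start of the diet". The Background gives the same limit. Under Participants, the related exclusion is "current treatment for ADHD that cannot be discontinued", so children on treatment that can be stopped may enter.
- **Primary outcome (Respondership).** "response to treatment will be evaluated by assessing the change in ADHD and emotion dysregulation symptoms at T0 and T1 or T4". There are six scales, three rated by parents and three by teachers. A 30% fall counts as response and a 30% rise as deterioration.
- **Prior beliefs.** Parents complete this form at T0 and T1. On the baseline form: "This measurement also will be used to examine successful randomization".
- **Use of the result.** In the 2nd phase section, non-responders and the deterioration group are advised to stop the diet and switch to care as usual. Under Data monitoring, the interim stopping rule is set on the percentage of responders across the dietary treatments (5%, against an expected 42%).

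**The concern.** T0 is the denominator of the percent change on every scale, so anything that moves T0 moves the child's response category. Two features of the timing can move it.

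First, parents who already know the diet may rate the starting point differently depending on which diet they drew. This can bias the comparison of elimination diet (ED) with healthy diet (HD), because the knowledge differs by arm. It also clouds the belief check: a difference in T0 beliefs could reflect the opened envelope and not a failure of randomization.

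Second, a child rated at T0 on medication and at T1 off it has two measurements under different conditions. A real improvement on the diet can be hidden, and a child who has not changed can look worse. This can happen in both diet arms. Its main effects are dilution of the ED-HD contrast and lower absolute response rates, and those rates drive the advice to stop the diet and the interim rule.

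**Working it through.** **1. The plan's own figure.** The article states power of 0.99 and 0.64 with 81 per arm (Table 4, scenarios 1 and 2). Whitehead's formula for the proportional-odds model is

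power = Φ( |log OR| × √[N/12 × (1 − Σp̄³)] − 1.96 ), with N = 162 and p̄ the mean category proportions of the two arms.

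- Scenario 1, Table 4 percentages: OR 3.62, Σp̄³ = 0.090. Φ(1.285 × √12.28 − 1.96) = Φ(2.55) = 0.995.
- Scenario 2, Table 4 percentages: OR 1.91, Σp̄³ = 0.070. Φ(0.646 × √12.55 − 1.96) = Φ(0.33) = 0.63.

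The Table 4 counts give 0.996 and 0.66. The stated power reproduces and is not in dispute; it presumes an undistorted baseline.

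**2. Order of disclosure and T0.** The intake plans the appointments and opens the envelope. T0 is a scheduled site assessment, and no earlier T0 is described. The natural reading is disclosure first, then T0. The text does not say so outright, and the flowchart is not available.

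**3. Size of a disclosure effect (illustration).** Suppose knowledge of the arm changes the parent's T0 score by a factor (1 + u), with T1 unaffected. The true reduction that registers as 30% is 1 − 0.7 × (1 + u):

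| u (assumed) | true reduction that registers as 30% |
|---|---|
| −10% | 1 − 0.63 = 37% |
| 0 | 30% |
| +5% | 1 − 0.735 = 26.5% |
| +10% | 1 − 0.77 = 23% |
| +20% | 1 − 0.84 = 16% |

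The documents give no value for u and no direction.

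**4. Medication timing.** T0 may fall on days −14 to 0, and medication may continue to day −7. The first 7 of the 14 days therefore allow a T0 on medication. T1 is off medication for children who follow the first-phase rule. Neither limit refers to the other.

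**5. Size of a medication effect (illustration).** Let medication lower the T0 score by a fraction m (assumed). For a true off-medication reduction d, the apparent reduction is 1 − (1 − d)/(1 − m). The true reduction needed to register 30% is 1 − 0.7 × (1 − m).

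| m | true 30% appears as | no change appears as | true reduction needed |
|---|---|---|---|
| 10% | 22% | 11% increase | 37% |
| 20% | 12.5% | 25% increase | 44% |
| 30% | 0% | 43% increase | 51% |
| 40% | −17% | 67% increase | 58% |

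An unchanged child passes the deterioration limit once 1/(1 − m) ≥ 1.3, that is m ≥ 23%.

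**6. Dilution (illustration).** Suppose a share f of each arm is moved out of its true category, half to non-responder and half to deterioration. Using the Table 4 percentages, power falls as follows:

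| f (assumed) | scenario 1 | scenario 2 |
|---|---|---|
| 0 | 0.995 | 0.63 |
| 10% | 0.965 | 0.49 |
| 20% | 0.88 | 0.37 |
| 30% | 0.74 | 0.27 |

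The documents give no value for f.

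**The case against.** Several stronger readings are tempting, and the documents do not support them.

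- *Every percent change is contaminated by disclosure.* Teachers are said only to be informed about the study, not told the diet. Disclosure bears on the three parent scales. Full response also needs a teacher scale at 30% or more, so a shifted parent baseline can produce a full responder only where a teacher scale already qualifies. It can still move a child between other categories.
- *Families who leave on hearing their diet break the intention-to-treat analysis because they lack T0.* Such a family would ordinarily lack T1 as well. An earlier T0 would not classify it by observed change; it would only supply a value for the missing-data methods the article names.
- *The belief check is void.* The form asks about dietary intervention and care as usual in general, and nothing shows that it separates ED from HD. The check is weakened, not destroyed. It also spans three groups, one of them self-selected, which re-ordering would not cure.
- *The two timing sentences contradict each other.* Each sets an outer limit, and both can be met together. The fault is that they are not linked.
- *Half of the children are rated on medication.* Seven of 14 days describes the calendar and says nothing about how many children are affected.

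Two further objections stand. Parents also rate T1 unblinded, so an earlier T0 removes only part of the expectation bias. And SWAN items run from 3 to −3, so a total can be near zero or negative. The percentage arithmetic above has a fixed meaning only if scores behave as ratio-scale.

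**Conclusion.** The point holds in limited form. A trial that follows the Procedures section exactly can compare an on-medication T0 with an off-medication T1 on all six scales. It will also probably collect parent T0 ratings with the arm known. The first follows directly from the text. The second is inferred from the order of steps, with the flowchart not shown.

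Disclosure can bias the ED-HD comparison through the parent scales, in a direction the documents do not fix. The medication mismatch is balanced in expectation by randomization, so it mainly dilutes the contrast and lowers absolute response; it does not favour an arm.

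The size of either effect cannot be estimated. The share of children medicated at T0, the usual day of T0, the effect of medication on the scores and the effect of disclosure on ratings are all absent. The tables show how sensitive the 30% limits are under stated assumptions and are not estimates. The sample size is unaffected. This should be changed because the remedy is cheap and the baseline feeds the primary outcome, the advice to continue or stop, and the interim rule.

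**What to change.** 1. Obtain the parent SWAN, SDQ and prior-belief forms before the envelope is opened, and state that order in Procedures. The parent questionnaires can be completed before or at the intake. Other T0 measures, such as the week of actigraphy and the three-day food record, need not all precede disclosure for this purpose. The cost is a re-ordering of steps and less time for families between learning the diet and starting it.
2. The T0 window and the medication-discontinuation sentence must be reconciled by the investigators so that T0 and T1 ratings are comparable. The clinical rule itself is theirs to set.
3. Record medication status at T0 for every child in the diet arms, including those already enrolled where it can be recovered. Add a sensitivity analysis of respondership that excludes, or adjusts for, children rated on medication at T0. The cost is one data item and one extra analysis, with some loss of precision if children are excluded.
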